### Existing MRE-prevention activities in Germany

In Germany, primary and secondary care providers have established so-called MRE-Networks in order to limit the spread of multi-drug resistant pathogens (MRE). There are currently 150 MRE-Networks across Germany, with every federal district (Bundesland) having at least one major MRE-Network [20]. In Baden-Wuerttemberg nearly every regional district has an established MRE-Network. The local health authorities are responsible for coordinating regular meetings between participating care providers across all health care sectors (outpatient and inpatient care). Activities include the implementation of national guidelines developed by the Robert-Koch-Institute, the support of intersectoral, MRE-based information exchange, screening of patients at risk of colonization, decontamination during or after an inpatient stay, education for patients and care providers as well as to strengthen the cooperation between health care providers and local health authorities.

### Recruitment

Patients will be allocated to either study group based on their GPs. GP practices will be predefined as either control or intervention practice based on their participation in the regional MRE-Network. The intervention group will only contain practices that partake in the MRE-Network Heidenheim, while the control group will include non-participating practices from Heidenheim as well as other districts. With the engagement of the physicians association Heidenheim (Kreisärzteschaft Heidenheim) in the conception of the project, we expect a high acceptance amongst GPs. The recruitment of practices is jointly carried out by the Association of Statutory Health Insurance Physicians Baden-Wuerttemberg (Kassenärztliche Vereinigung Baden-Württemberg) and the physician association Heidenheim.

The intervention phase will stretch over a period of 24 months and is preceded by a 6 months recruitment and preparation phase (also see Fig. 2).

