### Study design

In order to achieve these objectives the study will employ a controlled study design (A) with a time series analysis (pre-post comparison) on clinic and district level (B) (Fig. 1, Table 2). There is no randomization on practice or patient level. A detailed overview of the endpoints for analysis (A) and (B) can be found in under ‘Outcomes’.

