#### Sample size

The sample size was calculated to secure enough power for examining the effect of the intervention for both subgroups (MSSA and MRSA) on colonization status upon hospital admission (primary endpoint). We expect cluster effects to be relatively small as the introduction to decontamination measures will be carried out by link nurses who have received a standardized training. With the expected 13,260 Patients a power of 92% would be achievable, assuming that there are no cluster effects. Although the occurrence of a cluster effect cannot be excluded, we believe that with an eligible patient population of 13,260, potential reductions in power would still fall within an acceptable range (also see Fig. 3).

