### Statistical analysis

**The primary endpoint** (comparison of colonization rates prior to surgery) will be analysed separately for MRSA and MSSA using logistic regression modelling with GEE (Generalized Estimation Equation) correction to account for potential cluster effects. The power calculation (see section 2) was based on the commonly used significance levels for two-sided chi-square tests. Given the higher prevalence of MSSA, two different levels of significance were chosen for MSSA (0.001) and MRSA (0.049). **Analysis of secondary endpoints** will involve adjustment for covariates such as age and gender using logistic regression modelling with GEE correction. However, the interpretation of local significances is not designed to be strictly confirmatory. Due to the multitude of secondary parameters and the lack of a hierarchical structure, a correction for multiple tests is not necessary. Descriptive analyses are performed following scaling and observed data distribution.

**Qualitative data** from focus groups will be transcribed and then analysed using qualitative content analysis [23]. Data collection will continue until thematic saturation is reached. The resulting category system will help to understand the feasibility of the intervention in daily practice from the perspective of providers in outpatient and hospital care. It will thereby provide additional information to the patient perspective evaluated via questionnaire data. Additionally, all qualitative data systematically collected or observed during the study will be considered as data. This means that not only information from focus groups and questionnaires will be analysed, but also all data documented during hotline calls or observed during site visits. This data will be collected by study personnel in the Heidenheim Clinic via a logbook. Entries of free text will be categorized thematically. Data entries will then be analysed descriptively following observed data distribution. Quantitative analysis will be carried out in Microsoft Excel (Version 2010) und IBM SPSS Statistics (Version 25). For qualitative data analysis MAXQDA (Version 2018) will be used.

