**Subgroup analysis** is planned for patients from gynaecology as the criteria for initiating a decontamination procedure are mostly based on the recommendation of the supervising physician. Furthermore, the primary goal regarding this subgroup analysis is to extract prevalence rates – the success of the decontamination will most likely not be the main focus of the analysis. This is also linked to the small number of patients expected to undergo a decontamination procedure. All patients who are not undergoing a surgical procedure will be considered as a potential subgroup. This is due to the possibility of slight variation in the patient pathway as well as a different risk of complications upon follow-up. All other stratifications will be considered in the statistical model. The robustness of primary and secondary findings will be assessed through sensitivity analysis. Depending on the proportion of missing values, we will either use imputation or only complete data-sets.

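### Controls come partly from other districts while every intervention practice is in the Heidenheim network, so a district difference in carriage enters the primary contrast in either direction

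*Protocol article*

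**What the plan says.** **Allocation.** Under Recruitment, "GP practices will be predefined as either control or intervention practice based on their participation in the regional MRE-Network". For the intervention arm, "The intervention group will only contain practices that partake in the MRE-Network Heidenheim". For the comparator, "the control group will include non-participating practices from Heidenheim as well as other districts". Study design adds: "There is no randomization on practice or patient level".

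**Analysis.** Under Statistical analysis, the primary endpoint is analysed by logistic GEE, separately for MRSA (two-sided level 0.049) and MSSA (0.001). The GEE correction is there for clustering. Age and gender are named as covariates for the secondary endpoints; district is named nowhere. The subgroup paragraph adds "All other stratifications will be considered in the statistical model" and a general promise of sensitivity analyses.

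**Size.** Sample size states: "With the expected 13,260 Patients a power of 92% would be achievable, assuming that there are no cluster effects".

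**Context.** All patients are scheduled for a procedure at the one local hospital and swabbed there on admission (inclusion criteria; Hospital admission step). Matched control districts appear under Aim, for the insurance-data time series (B). The Discussion acknowledges selection bias from recruiting intervention practices through the network.

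**The concern.** The primary question is whether outpatient screening and decontamination lower carriage at admission. To answer it, the two arms should be alike apart from the intervention. Here the control arm has two parts. Heidenheim non-network practices share a district with the intervention practices. The other-district practices have no intervention practice in their district, so for them a district effect and an intervention effect are the same contrast.

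A GEE correction for clustering repairs standard errors; it does not remove a systematic difference between districts. If carriage is higher in the other districts, the pooled comparison shows a benefit that decontamination did not produce. If it is lower, a real benefit is diluted or lost. The protocol links the comparison to possible nationwide roll-out, so attribution matters.

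**Working it through.** **1. The plan's own figure.** The 92% power cannot be reproduced. The text gives no planning rates, no effect size and no arm split, and Fig. 3 is not shown. The calculations below therefore take 92% as given.

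**2. Inputs.**
- Total 13,260 (Sample size). Assumed 1:1, so 13,260 / 2 = 6,630 per arm; patients independent.
- Two-sided level 0.049 for MRSA, so z = 1.9686 (Statistical analysis).
- MRSA carriage of 1-2% (Background). This is a national population figure, not a planning rate and not a measure of variation between districts.
- f, the share of controls from other districts: not given, so varied.

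**3. Bias.** Let h be carriage in Heidenheim and o carriage elsewhere, with no intervention effect. The pooled control rate is (1 − f)h + f·o, so the spurious difference is d = f(o − h).

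P(reject) = Φ((d − z·SE0)/SE1) + Φ((−d − z·SE0)/SE1), with SE0 the pooled and SE1 the unpooled standard error.

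Example: h = 1.0%, o = 2.0%, f = 25%. Control rate = 0.75 × 1.0 + 0.25 × 2.0 = 1.25%, so d = 0.25 points. SE0 ≈ SE1 ≈ 0.183 points. The first term is Φ((0.25 − 1.9686 × 0.1832)/0.1832) = Φ(−0.60) = 0.273; the second is below 0.001. Total 27%.

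Rejection with no true effect (nominal 4.9%):

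| f | 1.0% vs 1.5% | 1.0% vs 2.0% |
|---|---|---|
| 5% | 5.1% | 5.8% |
| 10% | 5.8% | 8.6% |
| 25% | 10.6% | 27.3% |
| 50% | 27.3% | 73.3% |

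With o = h the rate stays at 4.9% for any f.

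MSSA at 0.001: assuming 20% versus 25%, rejection is 0.5% at f=10%, 6.5% at f=25% and 59% at f=50%, against nominal 0.1%. The 20-30% in the Background is for S. aureus overall, so this example is looser.

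**4. The opposite direction.** Take h = 1.5%, o = 1.0% and no effect. At f=25%, d = 0.25 × (1.0 − 1.5) = −0.125 points. A falsely favourable result then occurs in 0.5% of trials, below the nominal 2.45% per side. If instead a true effect takes carriage from 1.5% to 0.867% (the effect with 92% power at 6,630 per arm), the pooled control rate at f=25% is 0.75 × 1.5 + 0.25 × 1.0 = 1.375%, and power falls to 79%.

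**5. Power of the within-Heidenheim contrast.** Hold the effect that gives 92% at 6,630 per arm and reduce controls to 6,630 × (1 − f). MRSA uses 1.5% versus 0.867% at 0.049; MSSA uses 25% versus 21.6% at 0.001.

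| f | Heidenheim controls | MRSA | MSSA |
|---|---|---|---|
| 10% | 5,967 | 90.7% | 90.0% |
| 25% | 4,973 | 87.9% | 85.7% |
| 50% | 3,315 | 79.9% | 71.5% |
| 75% | 1,658 | 62.0% | 39.5% |

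MRSA control rates of 1% and 2% give 61-63% at f=75% and about the same elsewhere. With 2:1 or 1:2 arms, MRSA power at f=50% is 77% to 83%.

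**6. Whether the text already deals with it.** The stratification sentence does not name district. The matched districts serve series (B), for which Table 3 lists MRSA colonization only, so MSSA is not covered. The Discussion's bias statement concerns network recruitment, not the district make-up of the controls in comparison (A).

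**The case against.** The strongest reply is that material bias needs both a large f and a large district gap, and neither is documented. That stands. The 73% figure puts Heidenheim at the bottom of a national range and the other districts at the top, which no section supports. All patients use the same hospital and the same admission swab, so out-of-district controls are people who choose that hospital, not a sample of distant districts. What still differs is patient origin and outpatient care, which may bear on carriage.

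Three stronger readings are tempting, and the document does not support them:
- *That the 92% is wrong.* It belongs to the pooled comparison. The losses in step 5 apply only if the effect is estimated within Heidenheim, and no section commits to that.
- *That out-of-district controls are active network practices.* It is true that "In Baden-Wuerttemberg nearly every regional district has an established MRE-Network", but non-participating may govern both control sources, so their status is unclear. The network decontamination described takes place during or after an inpatient stay, not before admission. If it did lower carriage, the bias would run against the intervention.
- *That the design favours the intervention.* The direction is unknown.

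It can also be said that naming a sensitivity contrast is SAP detail. The contrast might be, but the composition of the control group is a design choice fixed in this document, and no later model can supply intervention patients from practices in other districts.

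**Conclusion.** The concern holds as a confounding risk of unknown size and direction. As written, the plan lets any district difference in admission carriage enter the primary contrast, and neither the general stratification and sensitivity wording nor series (B) removes it. Under the stated assumptions, the distortion is negligible at f of 5% or less (MRSA rejection at most 5.8% against 4.9%), modest at 10%, and potentially serious from 25% upward if the district gap is large. These are ranges under assumed arm sizes, independent patients and background prevalences, not estimates of this trial's error rate. The sponsor can largely settle the matter by stating f. It should be addressed, but it does not invalidate the design.

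**What to change.** - Keep the pooled primary contrast as planned.
- Code controls in two levels, Heidenheim non-network and other-district, by practice location.
- Pre-specify intervention versus Heidenheim non-network controls as the key sensitivity analysis, for both MRSA and MSSA.
- Report the carriage difference between the two control parts with its confidence interval.
- State the expected f and the power of the within-Heidenheim contrast at that f.
- Say clearly whether out-of-district controls may belong to another MRE-Network.
- State that if the two contrasts differ materially, the pooled result will not be attributed to the intervention alone, and define in advance what counts as material.

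**Cost.** One extra factor level and one extra contrast. Practice is the unit of allocation, so its location is known and no extra patients or data are needed. The within-Heidenheim contrast is less precise. It also leaves in place the self-selection of practices into the network, which still coincides with study arm and which the Discussion already acknowledges.

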**Fig. 2 Fig2:**
[figure not shown]
Timeline

### Participants

#### Inclusion and exclusion criteria

Patients aged 18 and above and scheduled for an elective procedures in the local community hospital are eligible for inclusion. Elective interventions from general surgery, accident surgery, urology and gynaecology as well as surgeries at high risk for infections such as installations of drainages, PEG tubes (percutaneous endoscopic gastrostomy), and stents will be considered. Yet only patients whose insurance companies agreed to partake in the study by signing selective agreements can be considered in the recruitment process. In the German Healthcare System, such agreements enable care outside the predefined care catalogues. Emergency patients are excluded from the study.

#### Sample size

The sample size was calculated to secure enough power for examining the effect of the intervention for both subgroups (MSSA and MRSA) on colonization status upon hospital admission (primary endpoint). We expect cluster effects to be relatively small as the introduction to decontamination measures will be carried out by link nurses who have received a standardized training. With the expected 13,260 Patients a power of 92% would be achievable, assuming that there are no cluster effects. Although the occurrence of a cluster effect cannot be excluded, we believe that with an eligible patient population of 13,260, potential reductions in power would still fall within an acceptable range (also see Fig. 3).

**Fig. 3 Fig3:**
[figure not shown]
Sample size: intervention and control group (over 2 years)

#### Patient pathway

##### (1) **Study inclusion and risk assessment** (intervention and control group)

All patients, irrespective of risk of S Aureus colonization will be screened for risk of colonization with MRSA according to criteria defined by the Robert-Koch Institute (RKI) in the medical consultation session roughly 5 weeks prior to hospital admission (also see Fig. 4).

**Fig. 4 Fig4:**
[figure not shown]
Patient pathway: intervention and control group

##### (2) **Early testing and decontamination** (intervention group only)

Patients in the intervention group will be tested for MRSA and MSSA by specifically trained medical assistants (so-called ‘Link Nurses’) in the GP practice approx. two weeks prior to surgery. Cultural specimens of both nares, the throat and any wounds will be sent to the central laboratory of the University Hospital Tübingen in order to achieve a uniform quality and thus comparability of test results. In normal cases there is sufficient time to await cultural test results before initiating decontamination. In case of urgency (time to surgery is less than 10 days) rapid preoperative screening of patients will be performed during the medical consultation session with the use of polymerase chain reaction-based diagnostic tests (PCR). The initiation of subsequent decontamination measures in the outpatient setting will be based on results from PCR swabs. Due to the high false-positive rates of PCR Test results, all swabs will also be tested culturally in the central laboratory in Tübingen [5]. Prevalence estimates will be based on cultural swabs only.

MRSA and MSSA positive patients will be instructed on decolonization measures by Link-Nurses at the respective GP practise. Decontamination measures will be carried out across a 5-day period by patients themselves in the home environment. Patients are asked to use an antibacterial wash lotion on a daily basis, nasal mupirocin ointment (3x per day), antiseptic mouth rinse (3x per day) as well as disinfection of commonly used objects as well as the living environment (daily). The decontamination regime for MRSA is in accordance with the most recent recommendations by the Robert-Koch Institute [5]. The decontamination regime for MSSA was largely adapted from MRSA. As a MSSA specific national recommendation is lacking, the decontamination protocol was created in accordance with relevant international publications and expertise of clinical hygienists [4, 7, 21, 22].

##### **(3) Hospital admission** (intervention and control group)

Upon admission all patients scheduled for elective surgery from both control and intervention groups receive a cultural swab of nares, throat and any wounds in order to assess the success of the decontamination (primary endpoint). In case the test result is positive, decontamination measures will be carried out in the hospital setting in accordance with the standard procedure in routine care.

##### (4) **Follow-up** (intervention group and control group)

Patients in the intervention group follow-up care will be provided by the GP, control patients will schedule follow-up appointments in the local community hospital.
Surveillance of surgical site infections (SSI) within 90 days after hospital dischargeControl swabs 3 and 6 months post discharge. The respective GPs will reach out to patientsAt follow-up visits Link Nurses provide patients with information on how to prevent recolonizationIn case of a positive test result for MRSA, decontamination according to routine care will be initiated

The modification of an allocated intervention is to be avoided. In some cases, however, the total of 5 days of decontamination may not be implemented for instance in case of urgency. This will not result in an exclusion of the specific patient in question. Change of study arm is not permitted during the study (intention to treat).

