**Methods:**

This study is a controlled interventional study (*N* = 13,260) with a pre-post comparison. The intersectoral intervention (over 2 years) will encompass the following elements: ambulatory detection and decontamination of MRSA and MSSA prior to elective surgery combined with a structured follow-up care. Patients from the control group will be screened in the hospital setting, in accordance with the standard operating procedure (SOP) in routine care. The primary endpoint is the reduction of MRSA and MSSA colonization upon hospital admission. Secondary endpoints are complication rate (SSI), length of stay, recolonization of patients (3 and 6 months after release), patient and provider satisfaction, patient compliance and cost development.

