## Background

*Staphylococcus aureus* (S Aureus) bacteria are detectable on the skin or mucus membranes of the nasal passage and pharynx in about 20 to 30% of the population [1]. Most of S Aureus isolates exhibit sensitivity to beta-lactam antibiotics (e.g. Methicillin or Oxacillin) and are therefore referred to as methicillin-sensitive S Aureus (MSSA). In contrast, methicillin-resistant S Aureus (MRSA) bacteria are resistant to these antibiotics. MRSA isolates are much rarer than MSSA, only affecting about 1 to 2% of the population in Germany [2].

During surgical interventions both bacterial strains (MSSA and MRSA) can cause infections as they gain access to other organs or tissues. If the infection occurs up to 30 days post-surgery and affects the incision or deep tissue at operating sites they are termed surgical site infections (SSI) [3]. Surgical site infections remain the second most common health-care associated infection (HAI) in Europe and the US [4]. SSIs are associated with prolonged hospital stays, additional physician visits, impairment of the healing process and elevated use of antibiotics [5]. The national guideline by the Robert Koch Institute (RKI) [6] on the prevention of SSI, recommends establishing screening and decontamination procedures for S Aureus, in particular for high risk surgical interventions. While MSSA is increasingly recognized as a risk factor internationally, evidence on the effectiveness of screening and decontamination protocols for MSSA is scarce and it is often not explicitly addressed in national guidelines [5, 6]. Correspondingly, preoperative screening and decontamination efforts in German routine care are targeted at MRSA only. Evidence suggests that decolonization regimes for MSSA can be protective against SSI, particularly since MSSA is a noteworthy contributor to SSI prevalence rates [7, 8].

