Unlike for MSSA; the evidence base on MRSA decolonization is more extensive. While the establishment of hospital based screening, isolation and decolonization routines may have contributed to a general decline of MRSA, Germany is still lagging behind when compared internationally [6, 9, 10]. The effectiveness and efficiency of universal screening regimes for MRSA have been documented in several studies, yet screening measures in German routine care are strictly risk based [11–13]. This may result in colonized patients without a corresponding risk profile to remain undetected. Furthermore, decolonization and hygiene measures are commonly implemented during an inpatient hospital stay [7, 11, 12, 14, 15]. With up to 90% of S Aureus cases already being detectable prior to hospital admission [16], shifting screening and decontamination to the primary care setting can provide an effective tool to prevent the introduction of MRSA to the hospital setting. To date only a limited number of studies have assessed the effectiveness of MRSA decontamination regimes in the home environment [14, 17]. Findings point to the importance of patient education and self-sufficiency as integral parts of successful decolonization as direct clinical supervision is lacking in the home setting [14, 17, 18]. Next to that, post-discharge follow-up and decontamination measures can lower the risk of SSIs for MRSA carriers as well as rehospitalisation [19]. In spite of the evidence, the absence of remuneration options has at least partly hampered a systematic prevention and treatment of MRSA colonization and associated complications (SSI) in Germany.

STAUfrei aims to fill these treatment gaps by implementing an intersectoral care pathway stretching from ambulatory screening and decontamination (independent of risk profile) to a structured follow-up care in the primary care setting. Remuneration options for preventative (screening and decontamination) and follow-up (re-)colonization and infection control) care in the outpatient setting is offered by the major health insurance funds in the district. In order to investigate possible advantages of this novel care pathway compared to the current standard operating procedure in routine care, the latter was chosen as a comparison. This is also linked to the overarching aim of a potential nation-wide implementation.

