## Methods/design

### Aim

The primary aim of the study is to reduce cases of MRSA and MSSA colonization upon hospital admission. Secondary objectives include prevention of postoperative complications (SSI) and recolonization through a structured follow-up care in the outpatient setting. Additionally, patient compliance, patient and provider satisfaction as well as cost developments will be evaluated.

In order to evaluate the effect of the intervention on a clinical and district level, we aim to carry out a time-series analysis with a pre-post comparison (see Table 1). On a clinical level routine data from the intervention phase (2019–2020) will be contrasted with historic routine data (2015–2018) from the local community hospital. The effect of the intervention will be evaluated both, in terms of clinical and health economic parameters. The district level analysis will be based on routine data from the health insurance fund (AOK Baden-Württemberg). The aim is to evaluate whether the (potential) positive trend in Heidenheim is also observable in other districts. Control districts will be matched according to socioeconomic and demographic aspects (e.g. number and size of hospitals in district, age structure, unemployment rate).

**Table 1 Tab1:** Primary and secondary objectives

Primary research question	
Does the implementation of measures in the primary care setting including ambulatory screening and decontamination reduce MRSA and MSSA colonization rates upon hospital admission?	
Secondary objectives	
Do primary care measures (patient supervision and support through GP practices pre- and post-surgery) reduce recolonization rates (MRSA) amongst patients who underwent elective surgery?	
Does a reduction in MSSA colonization upon hospital admission correlate with an improved quality of care measured by a reduction in surgical site infections, length of stay and rehospitalisation?	
Does the implementation of decontamination measures in the primary care setting lead to a reduction of associated costs for patients undergoing elective surgery?	
How is the feasibility of the intervention evaluated by participating GP practices?	
How do patients evaluate the feasibility of the decontamination in the home environment?	

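### Scheduled hospital follow-up of controls could enter the between-arm cost on one side only, and it limits what the 6-month MRSA result can claim

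*Protocol article*

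**What the plan says.** **Comparator.** The Background sets the new pathway against usual practice: "compared to the current standard operating procedure in routine care, the latter was chosen as a comparison". The Abstract (Methods) describes the intervention as "ambulatory detection and decontamination of MRSA and MSSA prior to elective surgery combined with a structured follow-up care". Of the controls it says only: "Patients from the control group will be screened in the hospital setting, in accordance with the standard operating procedure (SOP) in routine care".

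**Follow-up.** Step (4) of the patient pathway is headed for both groups. Intervention patients are followed by their GP; "control patients will schedule follow-up appointments in the local community hospital". The step then lists swabs at 3 and 6 months after discharge and states, for the case of "a positive test result for MRSA, decontamination according to routine care will be initiated". That item is not restricted to one arm.

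**Objective.** Table 1 (Aim) asks about recolonisation in these terms: "patient supervision and support through GP practices pre- and post-surgery) reduce recolonization rates (MRSA". Table 3 (Outcomes) lists MRSA recolonisation at 3 and 6 months as a laboratory endpoint. The secondary analysis "will involve adjustment for covariates such as age and gender using logistic regression modelling with GEE correction".

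**Cost.** Table 3 places secondary-care cost in the Heidenheim clinic routine data, which its footnote assigns to the group comparison and the time series. Primary-care cost appears only in the AOK-BW insurer data, which the same footnote assigns to the time series alone.

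**The concern.** Scheduled detection and treatment after discharge is named as part of what is tested, yet controls receive a version of it. Two results could be misread.

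- **Cost.** The Discussion expects outpatient cost to rise and secondary-care savings to offset it. If control follow-up visits are recorded in the clinic's cost data, they raise the control arm's secondary-care cost. The matching visits in the intervention arm take place at the GP, outside that source. The between-arm cost would then move in the hoped-for direction even if the intervention saved nothing.
- **Recolonisation at 6 months.** By then, MRSA positives found at 3 months have been offered decontamination in both arms. Read as an effect against routine care, the result leaves out whatever scheduled swabbing and treatment achieve, because controls had them too. Nation-wide implementation is the stated longer-term aim, so the label matters.

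**Working it through.** The plan gives no figure to reproduce here. It states no 3-month MRSA rate, treatment success, acquisition rate or visit cost, and it does not say whether recolonisation is counted in all patients or in prior carriers. Every input below is an assumption; only the order of magnitude of MRSA carriage has a source (Background: "MRSA isolates are much rarer than MSSA, only affecting about 1 to 2% of the population in Germany").

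**1. What the 6-month contrast contains**

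- Intervention arm: outpatient testing and decontamination before admission (pathway step 2, this arm only), then GP follow-up with swabs and treatment of MRSA positives.
- Control arm: routine care at admission, then scheduled hospital follow-up with swabs and treatment of MRSA positives.
- Routine care as the article describes it: risk-based screening (Background) and decontamination during or after an inpatient stay (section on existing MRE-prevention activities). No scheduled 3-month swab is described.

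The 3-month swab is taken before any follow-up decontamination; the 6-month swab is not.

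**2. Illustration of the 6-month effect**

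Let p be the share MRSA positive at 3 months, s the share of treated positives cleared, and r the new acquisition from 3 to 6 months, with s and r equal in both arms. Untreated positives persist and cleared patients stay negative.

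- With treatment at 3 months: p(1−s) + (1−p)r
- Without it: p + (1−p)r

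All patients, p = 2% (control) vs 1% (intervention), s = 50%, r = 0.25%:

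- As planned: control 0.02×0.5 + 0.98×0.0025 = 1.245%; intervention 0.01×0.5 + 0.99×0.0025 = 0.7475%. Difference 0.50 points, OR 0.60.
- No 3-month treatment in either arm: 2.245% vs 1.2475%. Difference 1.00 point, OR 0.55.
- Controls never found and treated, intervention treated: 2.245% vs 0.7475%. Difference 1.50 points, OR 0.33.
- Routine care finds and treats every control carrier at 3 months: identical to the planned contrast, so no gap.

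Varying s over 30%, 50% and 80% at r = 0.25%, the planned difference is 0.70, 0.50 and 0.20 points and the OR 0.57, 0.60 and 0.69. At r = 0 and s = 50% the OR hardly moves (0.495 at 3 months, 0.497 at 6 months).

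A higher-risk group, assumed 40% vs 20% at 3 months with r = 10%: for s = 30%, 50% and 70% the planned difference is 12, 8 and 4 points, against 24, 28 and 32 if controls had no scheduled treatment.

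**3. Cost**

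Extra clinic cost per control patient = f × 2 visits × attendance × cost per visit, where f is the share of controls followed. Assume attendance of 0.5 to 1.0 and 30 to 100 euros per visit:

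- f = 1: from 2×0.5×30 = 30 to 2×1.0×100 = 200 euros.
- f = 20 to 30% (S. aureus carriage in the Background): 0.2×30 = 6 to 0.3×200 = 60 euros.
- f = 1 to 2% (MRSA carriage): 0.01×30 = 0.3 to 0.02×200 = 4 euros.

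If the visits are not booked in the clinic data, the amount is zero.

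**The case against.** - **Nothing is claimed wrongly.** The comparator sentence concerns the pathway as a whole, and the recolonisation question in Table 1 does not mention routine care. Controls must be swabbed to measure the endpoint. This stands: the swabs are not a fault, and the point limits a conclusion only.
- **The distance from routine care is unknown.** The treatment itself follows routine care, and routine care includes some decontamination after discharge. This stands; the OR of 0.33 is an extreme bound, and the gap could be nil.
- **The effect on the planned odds ratio is small.** At low MRSA rates, treating both arms moves the OR only from 0.55 to 0.60 in the central case. The modelled direction is towards a smaller absolute difference, so it would not create a false benefit on recolonisation. This also stands.
- **The cost point is conditional.** An article may leave costing rules to a fuller document, and no sentence says that study visits enter the clinic's costs. This limits the point to a safeguard. The asymmetry of sources, however, is stated in Table 3 itself.
- **The follow-up text is loose.** The items on GPs reaching out and on Link Nurses fit the intervention arm better, and it is unclear whether all patients or only carriers are followed. The heading and the hospital-appointment sentence still cover controls.

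A reader might infer that the 6-month result isolates GP-based against hospital-based follow-up. It does not, because the arms also differ in testing and decontamination before admission. A reader might also infer that the 3-month swab should become the lead result. The Statistical analysis section sets no hierarchy among secondary endpoints, and the 3-month swab captures less of the post-surgical support that Table 1 asks about.

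**Conclusion.** The point holds as a minor one, with two parts.

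(a) **Cost.** As Table 3 is laid out, control follow-up visits booked in the clinic data would count in the between-arm cost with no counterpart for the intervention arm's GP visits. The direction would favour the intervention. The size is unknown; the assumed range of 0.3 to 200 euros per control patient shows only how far it depends on who is followed and what is booked. The article does not support saying that a spurious saving will occur.

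(b) **Recolonisation.** The 6-month MRSA result sets the full intervention pathway against routine admission care plus scheduled hospital follow-up and treatment. It should not be reported as an effect versus routine care without follow-up. The likely direction is a smaller absolute difference, of unknown size, under the assumption of equal treatment success and acquisition in both arms.

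The primary endpoint is measured at admission and is not affected. The 3-month swab precedes follow-up decontamination. No fault is shown for SSI or rehospitalisation.

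**What to change.** 1. Add one costing rule: exclude the protocol-driven 3- and 6-month follow-up visits and swabs from the between-arm secondary-care cost, or value them identically in both arms.
2. Report MRSA recolonisation at 3 and 6 months side by side as planned, with no lead time point, and note that only the 3-month swab precedes follow-up decontamination.
3. Describe the 6-month comparator as routine admission care plus scheduled hospital follow-up with treatment of MRSA positives, and make no claim against routine care without follow-up.

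The cost is one coding rule and some wording; no new data are needed. The downsides are a narrower secondary claim and possibly a smaller apparent hospital saving.
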